## GLOSSARY OF ABBREVIATIONS

|       |                                                              |
|-------|--------------------------------------------------------------|
| BASEC | Business Administration System for Ethical Committees |
| CRF   | Case report form                                      |
| FOPH  | Federal Office of Public Health                       |
| HRA   | Human Research Act                                    |
| HRO   | Ordinance on Human                                    |

# 1 BACKGROUND AND PROJECT RATIONALE

Cesarean delivery rates are increasing worldwide, representing 18.6% of deliveries in 2016. However, this figure varies depending on the analyzed region, hence ranging from 6% to 27.2% between the least and most developed regions, respectively. Despite being major surgery and associating far more maternal and neonatal risks and lacking from a demonstrated benefit for both mother or the child, this trend has been continuously reproduced in different locations. The reasons for this increase are multifactorial and not yet well understood. They may include changes in maternal characteristics (as increasing maternal age for the first pregnancy, for example) and in professional practice styles, growing legal pressure, economic, organizational, social or cultural factors.

This situation has brought up concerns to the attention of many healthcare professionals and policy-makers, who started searching for strategies to stop (or even invert) the drift that these rates were taking. Thus, several strategies were adopted, including auditing or educational approaches, the design of multiple studies or the modification of the standard of care in many situations, such as the management of women with previous uterine scars or the mode of delivery in breech presentations.

Induction of labor (IOL) procedures (whose incidence also increased during the past years) have been classically considered as responsible of a fraction of the augmented proportion of cesarean deliveries. The example on the figure on the right seems to agree with this idea, as induced deliveries nearly duplicate the cesarean

[figure not shown]

section rate of the spontaneously started labors. However, the evidence that supports the previous appreciation is based on retrospective observations which approached the issue as the contrast between the rate of cesarean deliveries in women who spontaneously started labor with those who required an IOL. Though, recent studies switched the perspective of the problem, prospectively comparing perinatal outcomes among women who were electively induced at certain gestational age to those who were expectantly managed (hence including women with spontaneous onset of labor, but also women induced for different causes lately). After assessing this strategy (i.e. elective IOL vs. expectant management) in several clinical scenarios, the obstetrical dogma claiming that “IOL increased cesarean section rates” was severely questioned.

Thus, the approach of electively inducing labor at certain gestational ages, in order to reduce the incidence of adverse obstetrical outcomes (where cesarean delivery is included), has been assessed in the settings of advanced maternal age, obesity or, mostly, pregnancies over 41 weeks of gestation. Most of these studies conclude that an active attitude towards IOL results, in these cases, in lower incidence of poorer results (including, in some of them, a diminution in intrauterine death rates), while the proportion of cesarean deliveries remains stable, or even decreases. The most recent example of this strategy has been the ARRIVE trial, where low-risk nulliparous women were randomly allocated to elective IOL at 39 weeks or to an expectant management group. The main outcome (a composite of neonatal results, including perinatal death) was similar for both groups, but a secondary analysis revealed that the proportion of cesarean deliveries was higher in those women assigned to the expectant management group than in the IOL cohort (22.2% vs. 18.6%, respectively,  $p < 0.001$ ). These results prompted some scientific societies, such as the Society of Maternal-Fetal Medicine (SMFM), to elaborate statements where they claimed reasonable to offer elective IOL at 39 weeks of pregnancy to women who met ARRIVE eligibility criteria.

Although this recent evidence might support IOL as a method of improving perinatal outcomes, other issues must be addressed. For example, the  $1.8^0_{\infty}$  absolute reduction in perinatal mortality after elective IOL at 41 weeks (compared to the expectant attitude) represents a requirement of more than 550

inductions in order to avoid one death. Consequently, this strategy would substantially increase the number of inductions in exchange of a discreet global benefit (perinatal mortality rate between 41 and 42 weeks is about  $0.5^0/_{00}^{23}$ ). Following the results of the ARRIVE trial, 27 inductions would be needed in order to avoid one cesarean delivery. Evidence regarding cost-effectiveness and potential complications of this increase in IOL procedures is still lacking, hence the results of these studies have to be carefully interpreted before fitting them into current guidelines.

Furthermore, women's opinions in the matter of induction of labor must surely be considered. In fact, many women are uncomfortable with the idea of facing an IOL and more than half of them would rather not repeat the experience in subsequent pregnancies. Therefore, any safety concern, especially when the benefit is limited, must be outweighed with maternal perceptions, choices and points of view.

An extremely polarized drift of all these circumstances might result in guidelines with universal recommendations of IOL at certain gestational ages, which will not be followed only by women who are against this policy and, due to their thoughts and beliefs, decide to *rebel* against the standard of care. So, to try to balance all these elements, it may be useful the development of a tool that aids in the decision-making process by differentiating:

- (a) women who will spontaneously trigger their deliveries (thus theoretically profiting from an expectant management), hence followed-up according to current clinical guidelines
- (b) women who will require IOL despite any period of expectancy, therefore with the need of a more individualized counseling and tailored prognosis concerning their options towards the end of their pregnancies.

The prediction of the spontaneous onset of labor becomes, then, the keystone of this approach. Many studies have tackled the idea of detecting features or biomarkers able to identify those women who will naturally start delivery and, mainly, three groups of variables have been analyzed:

- **Maternal characteristics** such as age, body mass index, parity, ethnicity or Bishop score;
- **Ultrasonographic features**, including cervical length or the presence of funneling;
- **Biochemical biomarkers** comprising the vaginal detection of fetal fibronectin.

Most of these studies have been performed to evaluate this issue in pregnancies arriving at 41 weeks, while a small sample of them were carried out at earlier gestational ages. Among all the assessed variables, cervical length and body mass index were the most evaluated features and those that showed a higher association with spontaneous onset of labor. Regarding fetal fibronectin, it failed to discriminate women among the groups. However, it was scarcely analyzed in this field, as the efforts were mainly focused in preterm delivery. Concerning, Placental Alpha Microglobulin-1, it has not been yet evaluated for the prediction of term labor.

Although some variables, such as cervical length or body mass index, have shown certain association with spontaneous onset of labor, none of the authors have evaluated the association with a problem-solving approach, assessing the diagnostic accuracy of the found connections, thus without being able to succeed in transferring their research into clinical practice.

A biomarker that is gathering interest is the evaluation of cervical consistency. Traditionally included as one of the parameters evaluated in Bishop score, it has never achieved relevance as a predictor neither of preterm delivery nor of spontaneous onset of labor. One of its main flaws is its high subjectivity, which leads to a very low reproducibility. However, different authors have started to focus on cervical consistency as a marker of preterm delivery, assessed either by ultrasound (by means of the cervical consistency index) or using aspiration devices, as the one developed Switzerland and commercialized by Pregnotia® AG (Information data sheet available as Appendix 2). Both of these techniques have shown that cervical consistency decreases with ongoing pregnancy, and the ultrasonographic evaluation has also been shown to be a potential predictor of preterm delivery (but not of the result of induction of labor), while Pregnotia® AG's device is currently being tested for these indications (SOFTCERVIX study - EUDAMED CIV-13-11-011694. Nevertheless, they have never been tested to evaluate the spontaneous

onset of labor. The Pregnotia System is used within the terms of its CE mark. It was certified by TUEV SÜED 0123, CE CERTIFICATE NR. PROBE: G1S 106145 0004 Rev. 00, CE CERTIFICATE Nr, CONTROL UNIT: G2M 106145 0003 Rev .01

It is unlikely that a single variable will explain and perfectly classify women into the two groups of interest, as onset of labor is still a poorly known issue and probably related to many processes. Hence, the development of studies with the objective of prediction is mandatory, while the multifactorial characterization of the outcome needs to be addressed by the multiple and simultaneous evaluation of many of the features that may be related to the effect of interest, supported by an adequate statistical layout and design.

## 2 PROJECT OBJECTIVES AND DESIGN

### 2.1 Hypothesis, primary and secondary objectives

#### *Hypothesis*

The evaluation of different clinical features, together with the ultrasonographic assessment of local cervical conditions and the estimated fetal weight, combined with the biochemical determination of fetal Fibronectin and Placental Alpha Microglobulin-1 in vaginal secretions will provide the probability of spontaneous onset of labor during the remaining days of pregnancy, hence allowing the discrimination between those women who will spontaneously trigger their deliveries from those who will require an induction of labor.

#### *Primary objectives*

1. To evaluate the performance, at 385/7-39 weeks of pregnancy, of different features in predictive models, designed to evaluate the probability of spontaneous onset of labor.

#### *Secondary objectives*

1. To analyze the individual accuracy of each of the evaluated characteristics at 385/7-39 weeks of pregnancy to diagnose the onset of spontaneous labor.
2. To establish the influence of each variable and the predictive models in the daily probability of spontaneous onset of labor after 385/7-39 weeks of pregnancy.
3. To analyze the individual accuracy of each of the evaluated characteristics at 39 and 40 weeks of pregnancy to diagnose the onset of spontaneous labor within 1 or 2 weeks.
4. To evaluate the performance, at 39 and 40 weeks of pregnancy, of different features in predictive models, designed to evaluate the probability of spontaneous onset of labor within 1 or 2 weeks.
5. To establish the influence of each variable and the predictive models in the daily probability of spontaneous onset of labor within 1 or 2 weeks after 39 and 40 weeks of pregnancy.

## 2.2 Primary and secondary endpoints

| VARIABLE TYPE                                      |  | VARIABLE AND SOURCE OF INFORMATION                                                                                                                                                                 |                       |
|----------------------------------------------------|--|----------------------------------------------------------------------------------------------------------------------------------------------------------------------------------------------------|-----------------------|
| Main outcome (1)
(logistic regression analysis) |  | Spontaneous onset of labor between 39 and 41 3/7 weeks of pregnancy
vs.
Induction of labor between 41 3/7 and 42 weeks of pregnancy due to gestational age             |                       |
|                                                    |  | Gestational age at spontaneous onset of labor (days after last menstrual period)                                                                                                                   |                       |
| Main outcome (2)
(survival analysis)            |  | Gestational age at spontaneous onset of labor (days after last menstrual period)                                                                                                                   |                       |
| Censorship                                         |  | Induction of labor due to maternal or fetal indication, different from gestational age.
Prelabor rupture of membrane without spontaneous onset of labor after 12 hours of expectant management. |                       |
| Predictors                                         |  |                                                                                                                                                                                                    |                       |
| Clinical                                           |  | Maternal age (years)
Maternal height (cm)
Closest to admission maternal weight (kg)
Previous vaginal deliveries
Previous cesarean deliveries
Expected delivery date                 |                       |
|                                                    |  |                                                                                                                                                                                                    |                       |
| Ultrasonographic                                   |  | Uterine cervical status (Bishop score)                                                                                                                                                             | Cervical digital exam |
|                                                    |  | Cervical length (mm)
Head to internal cervical os distance (mm)
Posterior cervical angle (degrees)
Cervical consistency index (%)                                                         | Transvaginal scan     |
|                                                    |  | Estimated fetal weight (kg)                                                                                                                                                                        | Transabdominal scan   |
|                                                    |  |                                                                                                                                                                                                    |                       |
| Biochemical                                        |  | Fetal Fibronectin (ng/mL) in vaginal secretion
Placental alpha macroglobulin 1 in vaginal secretion                                                                                             | Vaginal examination   |
| Biophysical                                        |  | Closing pressure (Cervical Stiffness Index, mbar)
obtained by Pregnotia System as a marker of cervical stiffness                                                                                | Cervical examination  |

Review of clinical records

385/7-396/7 weeks

## 2.3 Project design

Prospective international observational study with women enrolled at 385/7-396/7 weeks of gestation, who will deliver in the Maternity Unit of the Hôpitaux Universitaires de Genève and in the Frauenklinik of Basel.

### 3 PROJECT POPULATION AND STUDY PROCEDURES

#### 3.1 Project population, inclusion and exclusion criteria

##### ELIGIBILITY CRITERIA

Pregnant women at 385/7-39 weeks of gestation who will deliver at the *Hôpitaux Universitaires de Genève*, Switzerland.

##### INCLUSION CRITERIA

- Alive fetus
- Singletons
- Cephalic presentation
- Intact membranes
- Gestational age  $\geq 38^{5/7}$  weeks

##### EXCLUSION CRITERIA

- Fetal malformations
- Symptomatic uterine contractions
- Contraindication for vaginal delivery
- Medical indication of induction of labor or elective cesarean delivery
- Maternal desire to induce labor
- Maternal negative to enrollment
- Language barrier
- Inability to give consent

Specific Exclusion Criteria for Pregnotia System (if any of these criteria is present, the measurement of cervical stiffness using Pregnotia aspiration device will not be performed):

- Müllerian anomalies with two cervixes
- Severe vaginal bleeding
- Cervical dilatation
- Known HIV
- Visible, symptomatic cervical or vaginal infections
- If one of the following conditions is present on the cervix at the 12 o'clock position:
  - o Nabothian cyst
  - o Cervical myomas
  - o Cervical condylomas
  - o Squamous intraepithelial lesion
  - o Conization/LEEP2/LLETZ3
  - o Cervical endometriosis
  - o Cervical tears
  - o Cervical dysplasia
  - o Large ectopy, for which it is not possible to find a suitable location near the ectopy where native tissue is present
  - o Large scar tissue, for which it is not possible to find a suitable location near the scar where native tissue is present.

### SAMPLE SIZE

According to our data, approximately 78% of women will start their labor spontaneously before 41 weeks, meaning that 22% will have an induction of labor for medical reasons other than gestational age. Hence, considering 10 events (spontaneous onset of labor) for each of these 15 variables, and doubling this quantity for the elaboration of two different models, 13 participants will be required for each of these variables, hence 390 women are needed. Assuming a 10% rate of women with missing values in at least one predictor, 429 **patients** are needed.

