## 4 STATISTICS AND METHODOLOGY

### 4.1. Statistical analysis plan

#### MAIN ANALYSIS

The main outcome (spontaneous onset of labor vs. induction of labor between 41 and 42 weeks of pregnancy due to gestational age) will define two groups. The distribution of continuous or categorical variables among the units will be compared using Student's T test or Fischer's exact test, respectively. Two-sided significance level was set to 0.05.

A model of prediction of the binary outcome will be elaborated using stepwise backward and forward logistic regression analysis, including all analyzed features (gestational age at data collection will be included as an independent variable). To add or remove variables from the model, p-values of 0.05 or 0.10 will be used, respectively. Goodness-of-fit of the model will be evaluated using Hosmer and Lemeshow test and, if multiple models are achieved, the best one will be selected searching parsimony and following Akaike's Information Criterion. Area under the Receiver-Operating Characteristics curve will be used to assess predictive ability of the model. This value will be also calculated using bootstrapping resampling methods (1000 repetitions) to internally validate the results. As only a subset of the sample will have the measurement of cervical stiffness using Pregnotia device (as this assessment was lately introduced), a secondary analysis (following the same principles of the main analysis) will be performed. A correlation analysis will be carried out comparing cervical consistency index evaluated by ultrasound with cervical stiffness assessed using the aspiration device, as both measurement evaluate the same biophysical characteristic of the cervix.

The probability of spontaneous onset of labor for each day after the analysis will be evaluated using survival regression models. The data will be described using Kaplan-Meier's non-parametrical survival function and the predictive model will be estimated using stepwise backward and forward Cox's regression (proportional hazards model). As mentioned before, data regarding women whose labors have been induced due to maternal or fetal indication (different from gestational age) or with prelabor rupture of membrane without spontaneous onset of labor after 12 hours of expectant management will be censored at the time of admission for these causes.

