## 8 FUNDING / PUBLICATION / DECLARATION OF INTEREST

The developers of fetal Fibronectin determination kits (Hologic®) will provide them, along with the analyzers at no cost for the researchers. Funding and supplies support will be asked to the developers of Placental alpha macroglobulin 1 determination kits (Qiaogen®).

Regarding the collaboration with the enterprise “Pregnotia AG®”, which will be providing the device for the measurement of cervical stiffness, a collaboration contract has been established. One Pregnotia Control Unit , as well as 240 disposable Pregnotia Probes, will be provided free of charge for the conduct of the research.

Both enterprises have been informed that the study protocol will be published, as well as the conclusions of the research, whatever are the results. The design of the study, the data collection, analysis and publication are an exclusive responsibility of the researchers and no interference from the enterprises is expected. Data will not be shared, and the companies will only know the results once the analysis has finished.

The researchers are workers paid by the institutions involved in the study and will not receive any compensation for participating in the study. Once collaboration contracts are established with any of these two companies, SwissEthics will be immediately informed.

The contract regarding multicentric collaboration is attached to this protocol.

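### The sample size counts events on the majority outcome; the gestational-age induction group that limits the main logistic model is never sized and gives at most 5.7 women per variable, not 10

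*Protocol*

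**What the plan says.** Protocol section 3.1 (Sample size) starts from local data: "approximately 78% of women will start their labor spontaneously before 41 weeks". It gives the rest as "22% will have an induction of labor for medical reasons other than gestational age". It then applies a rule of ten events per variable, "considering 10 events (spontaneous onset of labor) for each of these 15 variables, and doubling this quantity for the elaboration of two different models", and concludes that "13 participants will be required for each of these variables, hence 390 women are needed". A 10% allowance for missing predictors brings this to 429.

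Section 4.1 (Main analysis) defines the binary main outcome as "spontaneous onset of labor vs. induction of labor between 41 and 42 weeks of pregnancy due to gestational age". Section 2.2 lists inductions for maternal or fetal indications under censoring, so those women fall in neither group of the binary outcome. Section 3.3, item 6, expects women who have not laboured, and who have no reason for earlier delivery, to be scheduled for induction at 41 to 42 weeks.

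Section 4.1 enters all features into stepwise logistic selection and states that "gestational age at data collection will be included as an independent variable". Cervical stiffness, measured only in a subset, goes to a secondary analysis. The area under the ROC curve is to be validated internally with 1000 bootstrap repetitions. The survival analysis, a Cox model for gestational age at spontaneous onset, is main outcome (2) in section 2.2.

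**The concern.** In a binary logistic model the information per candidate predictor is governed by the smaller outcome class, whichever class is called the event. The Protocol counts the larger one. The smaller class, women induced because of gestational age, does not appear in the calculation and has no expected frequency anywhere in the document. The only sentence that could supply one describes the remaining 22% as induced for other reasons, which conflicts with the outcome definition in sections 2.2 and 4.1 and with the induction pathway in section 3.3.

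This paragraph is the only justification of the sample size. If the smaller class is sparse, stepwise selection over about 15 candidates tends to pick an unstable set of predictors and to report a discrimination that is too favourable. The study aims to separate women who will labour spontaneously from those who will need induction, and it is this second group that is left uncounted.

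**Working it through.** **Inputs.** From section 3.1: 78% spontaneous onset before 41 weeks, 22% remainder, 10 events per variable, 15 variables, doubling for two models, 10% missing predictors. From section 4.1: the two outcome groups. The share of gestational-age inductions is not given, so a range is assumed below.

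**Reproducing the plan's figure.**
- Participants per variable: 10 / 0.78 = 12.8, rounded up to 13.
- 13 × 15 = 195; 195 × 2 = 390.
- 390 × 1.10 = 429.

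Both stated totals reproduce exactly. The multiplication is sound; the question is which class was counted.

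**Number of candidates.** Section 2.2 lists 15 predictors, including cervical stiffness. In the main model stiffness drops out (14 left) and gestational age at collection comes in, giving 15. So 15 is a fair divisor.

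**Support on the class the plan counts.** 0.78 × 390 = 304 spontaneous onsets; 304 / 15 = 20 per variable. This is the relevant count for the Cox model.

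**Support on the class that limits the logistic model.**
- Read literally: 100% − 78% − 22% = 0%, so no comparators.
- Upper bound, all 22% taken as gestational-age inductions: 0.22 × 390 = 85.8; 85.8 / 15 = 5.7 per variable.
- Assumed shares of the 390:

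| Gestational-age inductions | Women | Per variable (15) | Parameters at 10 per parameter |
|---|---|---|---|
| 22% (upper bound) | 85.8 | 5.7 | about 8 |
| 15% | 58.5 | 3.9 | 5 to 6 |
| 10% | 39 | 2.6 | about 4 |
| 5% | 19.5 | 1.3 | about 2 |

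**Why 22% is an upper bound.** Women who have not laboured before 41 weeks include those induced for medical reasons, those who labour spontaneously later, and the gestational-age inductions. Section 2.2 counts spontaneous onset up to 41 weeks and 3 days, which moves further women into the majority class.

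**The case against.** The strongest defence is that spontaneous onset is the proper event for the survival analysis, which is also a main outcome. With about 304 events the Cox model has twice the support the rule asks for. That stands, and it confines the fault to the logistic model.

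A second defence is that the Protocol plans parsimony, selection by Akaike's criterion and a bootstrap of the area under the curve. These help to gauge optimism. They do not supply the missing comparators, and the text does not say that variable selection is repeated in each bootstrap sample.

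A reader might also infer stronger charges that the document does not support:
- **That the comparison group is really empty.** Zero is only the literal consequence of a sentence that appears mislabelled. Sections 2.2, 3.3 and 4.1 all provide for gestational-age inductions. Their number is unstated, not nil.
- **That doubling for two models achieves nothing.** Its rationale is weak, since no separate sample per model is described, but it does raise the total from 195 to 390. At 195 women the Cox count would be 152 / 15 = 10.1 per variable instead of 20. The 5.7 above already includes the benefit of doubling.
- **That there are 16 candidates in the main model.** Stiffness leaves as gestational age at collection enters, so the count stays at about 15.
- **That the "240 disposable Pregnotia Probes" in section 8 cap the stiffness analysis.** They are described as supplied free of charge; the Protocol does not say that no more can be obtained.

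**Conclusion.** The point holds for the main logistic model. The Protocol's target of 10 per variable is calculated on the wrong class, and no reading of its 78% and 22% reaches 10 on the right one: the ceiling is 86 comparators, or 5.7 per variable. Plausible lower shares give 3.9 to 1.3, but these rest on an assumed range of 15% to 5%, because the Protocol gives no figure. The 22% sentence contradicts the outcome definition and must be corrected in any case.

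This is a fault in the quantity counted, not in the arithmetic. It does not show that the study as a whole is too small, nor that the order of the main outcomes should change: the Cox model is well supported by the same 390 women. All figures take the Protocol's own rule of 10 per variable as the yardstick.

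**What to change.** 1. In section 3.1, correct the sentence on the remaining 22% and state, from the centre's own data, the expected share of women induced because of gestational age, separately from medical inductions and later spontaneous onset.
2. Restate the logistic model's events per variable on that smaller group. Justify 390 by the Cox event count (about 304 events, 20 per variable) instead of by the number of models, so that the total keeps a stated derivation.
3. In section 4.1, replace stepwise selection over all features in the logistic model with a pre-specified candidate set that the comparator count supports (about 8 parameters at 86 comparators, about 4 at 39), or use penalised estimation. Repeat the whole model-building procedure inside each bootstrap sample.

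The cost is Protocol wording and one look-up in local data. No additional women are needed and the main outcomes keep their order. The downside is that the stated support for the logistic model becomes less favourable.
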